**Diagnosis:**

For the diagnosis of the patients with cervical radiculopathy clinical predictor rule will be applied consisting of Spurling’s test, Distraction test, ULNTT for median nerve and ipsilateral neck rotation [^23^](#_ENREF_23). Radiological imaging such as MRI will also be used for diagnosis.

**Constraints:**

Patient regularity and drop out might be a major constraint as my patient population ranges between age of 35-50, individuals in this age have a busy work routine hence once patient feels a little relief, he feels boredom visiting hospital or often leave from work place is an issue, however this issue will be tried to resolve by asking them about their will to complete the study and writing an official letter to their work place if needed and applicable.

# **Outcome measures:**

# The main outcome will be the effectiveness of neural mobilization technique on pain intensity measured on VAS, endurance measured by cranio cervical flexion test and range of motion measured on inclinometer. Secondary outcomes will be to see the effectiveness of conservative treatment and measuring the effects of treatment on quality of life [^24^](#_ENREF_24).

## Baseline measurements:

Patient age, gender, occupation, duration of pain, hypertension, heart disease, smoking and diabetes mellitus history will be noted at the time of recruitment. Further baseline pain, ROM, endurance, quality of life will also be noted.

## Visual analogue scale:

Visual analogue scale will be used to assess level of pain before, after and during the course of study.

## Inclinometer:

Inclinometer will be used to measure the ROM.

## Neck disability index (NDI):

Neck disability will be assessed by using neck disability index [^24^](#_ENREF_24).

## Cranio-cervical flexion test:

Cranio-cervical flexion test will be used to assess the neck endurance

Measurements will be taken at three levels before treatment, during treatment and at the end of treatment and a follow up reading to confirm the long lasting effect of the respective treatment [^25^](#_ENREF_25).

**SF-36:**

Improvement in quality of life will be assessed by using SF-36. That includes physical functioning, bodily pain, role limitations due to physical health problems, role limitations due to personal or emotional problems, emotional well-being, social functioning, energy/fatigue, and general health perceptions [^26^](#_ENREF_26)^,^ [^27^](#_ENREF_27).

**Data analysis procedure:**

Data will be analyzed on SPSS version 21 and MS Excel 2010. Descriptive analysis (mean, median, mode, variance, standard deviation) will be performed for quantitative data i.e. continuous and discrete variables. Frequencies and percentages will be calculated for categorical and nominal data. For graphical representation, continuous and discrete variables will be presented with histograms with normal curve and categorical and ordinal data will be presented in form of bar and pie charts.

Independent samples t-test and Man Whitney test will be used accordingly for between group comparisons. Repeated measure ANOVA will be used for within group analysis.

Inferential statistics will include independent samples t test and Man Whitney test at various levels of assessment for between group comparison while Freidman and repeated measure ANOVA will be performed for within group analysis separately. Excel 2010 will be used for scatter plotting and routine calculations.

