**Randomization:**

Randomization sequence will be created by using Excel 2016 with a 1:1 allocation using simple randomization by an independent researcher. Patients will be divided into two treatment groups, group A and group B randomly.

Patients will be allocated to two groups by concealment of allocation through sealed envelopes.

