**Group B (control group):**

In group B conservative treatment will be given which will include cervical isometrics exercises with 10 repetitions in each direction with 5 seconds hold will also be given. Isometric exercises will be performed with the patient in sitting position 3 sets of these exercises will be performed with the rest period of 30seconds.

All the subjects will be given hot packs for 10 minutes prior to the treatment.

Subjects having the same baseline will be given treatment for 12 sessions (3 times per week for 4 weeks). Pre assessment will be done at baseline, second assessment will be done after 2 weeks and final post assessment will be done at the end of 12^th^ session in 4^th^ week.

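### The arms are compared without baseline adjustment although baseline values are collected before allocation: the test is valid, but precision is given up that an ANCOVA would recover at no cost

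*Protocol*

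**What the plan says.** The protocol's section on the data analysis procedure gives the between-group method twice: first "Independent samples t-test and Man Whitney test will be used accordingly for between group comparisons", then "Inferential statistics will include independent samples t test and Man Whitney test at various levels of assessment for between group comparison". For the repeated readings it says "Repeated measure ANOVA will be used for within group analysis", and it adds the Friedman test for the same within-group purpose. It names no covariate, change score, ANCOVA or mixed model for comparing the arms.

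The outcome section lists the main outcomes as "pain intensity measured on VAS, endurance measured by cranio cervical flexion test and range of motion measured on inclinometer". The section on baseline measurements says "Further baseline pain, ROM, endurance, quality of life will also be noted", so every main outcome has a baseline value. The timing is fixed under Group B: "Pre assessment will be done at baseline, second assessment will be done after 2 weeks", with a final assessment at the end of week 4. Under concealment of allocation, the assessor pretests the participant before an envelope is assigned, so these are true pre-randomisation values.

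Randomisation is described as "1:1 allocation using simple randomization by an independent researcher". No stratification or minimisation on baseline severity is mentioned. The envelopes are made half for each treatment, which fixes the arm totals but does not balance baseline scores.

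**The concern.** The comparison of the two arms is the trial's objective, and the most useful covariate for it, the baseline value of the same outcome, is already in the data set. A two-sample test at week 4 ignores it. This has two consequences.

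- **Precision.** The part of the week-4 variation that baseline explains stays in the error term, so the confidence interval is wider than it need be.
- **Imbalance.** With 44 per arm and no stratification, the arms will differ somewhat at baseline by chance. The unadjusted week-4 difference carries a share r of that difference, where r is the correlation between baseline and week 4.

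The lost precision matters more because the protocol names dropout as a possible major constraint, while the sample-size paragraph shows no allowance for it.

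**Working it through.** **Inputs from the protocol (sample size section).** Means and SDs 3.35 (1.49) and 4.45 (1.63); effect size 0.70; significance level 0.05; power 90%; 44 per arm. Sidedness is not stated.

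**Assumptions, not in the protocol.** r = 0.3, 0.5 and 0.7, with equal SDs at baseline and week 4. Loss leaving 37 per arm, that is 7/44 = 16%; the constraints section gives no dropout rate.

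**1. The plan's own figure.**
- Pooled SD = √((1.49² + 1.63²)/2) = 1.562.
- d = (4.45 − 3.35)/1.562 = 1.10/1.562 = 0.704.
- Noncentral-t power of a two-sided two-sample t-test at d = 0.70 and 44 per arm is 90.1%, so the 88 reproduces. A one-sided test would need 36 per arm and does not fit.

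The sample size is therefore correct for the unadjusted t-test.

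**2. Gain from adjustment.** ANCOVA multiplies the error variance by 1 − r², so the effective effect size is 0.70/√(1 − r²). The confidence-interval half-width is 1.96 × 1.562 × √(2(1 − r²)/44), in the units of the planning means.

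| | Unadjusted | r = 0.3 | r = 0.5 | r = 0.7 |
|---|---|---|---|---|
| Variance factor | 1 | 0.91 | 0.75 | 0.51 |
| Effective d | 0.70 | 0.734 | 0.808 | 0.980 |
| Power, 44 per arm | 90.1% | 92.5% | 96.3% | 99.5% |
| Power, 37 per arm | 84.4% | 87.6% | 92.9% | 98.6% |
| 95% CI half-width, 44 per arm | 0.65 | 0.62 | 0.57 | 0.47 |

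Put another way, an adjusted analysis matches the precision of 44 unadjusted patients per arm with 44 × (1 − r²), rounded up: 41, 33 or 23 per arm.

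**3. Chance imbalance.**
- The SE of the baseline difference is √(2/44) = 0.213 SD.
- An imbalance above 0.3 SD in either direction lies 0.3/0.213 = 1.41 SEs out, which has probability of about 16% for each outcome.
- Such an imbalance shifts the unadjusted week-4 difference by r × 0.3 SD = 0.09, 0.15 or 0.21 SD. Multiplied by 1.562, this is 0.14, 0.23 or 0.33 points against the planned 1.10.

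**The case against.** **The planned test is valid and the trial was sized for it.** Over randomisations the unadjusted t-test keeps its 5% type I error and is unbiased, and its interval already allows for chance imbalance. Nothing in the protocol is false or contradictory on this point. All of that stands, so the point concerns efficiency and not error.

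**Adjustment could sit in an unseen statistical analysis plan.** This carries only limited weight. The protocol does not leave the between-group method open; it names unadjusted tests twice.

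**The gain depends on r.** This stands. At r = 0.3 it is about 2.4 points of power with 44 per arm.

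A reader might also infer stronger things, which the documents do not support:

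- *That the trial runs an inflated false-positive rate.* If the imbalance happens to sit at its 95% limit (1.96 × 0.213 = 0.42 SD), the conditional false-positive rate is about 7.5%, 12% or 19% for r = 0.3, 0.5 or 0.7. If the imbalance goes against Group A, conditional power is about 77%, 64% or 46%. But an imbalance that large in a given direction arises in only 2.5% of trials. With no imbalance at r = 0.5, the conditional false-positive rate is about 2.2%. The average over all imbalances is 5%.
- *That the choice between t-test and Mann-Whitney is made after seeing the data.* The protocol gives no such rule. Its wording may simply mean by type of variable, since the text just before it separates continuous from categorical and ordinal data.
- *That raw visit scores are certainly what is tested, or that a baseline test is certainly planned.* The phrase "independent samples t test and Man Whitney test at various levels of assessment for between group comparison" makes visit values the likelier reading and could include baseline, but it says neither outright.

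**Conclusion.** The point holds as a free improvement. The stated between-group analysis is valid and meets 90% power with 44 per arm and no dropout, but it leaves unused the baseline values that the trial collects for all its main outcomes.

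The size of the gain rests on the assumed r: modest at 0.3, substantial at 0.5 and above. Its practical value is as a margin against losses for which the sample size makes no stated allowance. At the assumed 37 per arm, the unadjusted test falls below the planned power, while ANCOVA stays above it at r = 0.5 or higher, though not at r = 0.3. Adjustment also removes the baseline imbalance from the estimate, so the result does not need to be argued over if the arms happen to start apart.

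**What to change.** In the protocol's data analysis procedure, state that each continuous main outcome will be compared between the arms by ANCOVA of the week-4 value on group and the baseline value of the same outcome, reported as an adjusted mean difference with its 95% confidence interval. Keep the Mann-Whitney test as a sensitivity analysis. In the sample size section, keep 88 patients and describe the 90% as the conservative figure for an unadjusted comparison.

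A mixed model covering weeks 2 and 4 with the baseline value as covariate is an option, but the point does not depend on it.

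The cost is two or three sentences. No new measurements, patients or software are needed.

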**OBJECTIVES**

The objective of the study was to compare the effectiveness of neural mobilization technique with conservative treatment on pain intensity, cervical range of motion, disability, cervical muscle endurance and quality of life

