**Group A (Experimental group):**

In group A neural mobilization technique with sliding of median nerve will be applied with 3 seconds hold in each repetition, Neural mobilization will be done according to technique described by David Butler [^22^](#_ENREF_22). Subject will be placed in supine position and slider neural mobilization of the median nerve will be given. In this group conservative treatment which will include cervical isometrics exercises with 10 repetitions in each direction with 5 seconds hold will also be given. Isometric exercises will be performed with the patient in sitting position.

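### The secondary outcome on the effectiveness of conservative treatment cannot be answered: both arms receive that treatment, and only within-group tests address it

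*Protocol*

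**What the plan says.** Under Objectives, the aim is comparative: to "compare the effectiveness of neural mobilization technique with conservative treatment on pain intensity" and on four further measures. The Outcome measures section then adds an aim of another kind: "Secondary outcomes will be to see the effectiveness of conservative treatment and measuring the effects of treatment on quality of life".

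The two arms share the treatment named there. Group B receives isometric neck exercises as its conservative treatment. Group A receives neural mobilization and also the exercises: "In this group conservative treatment which will include cervical isometrics exercises with 10 repetitions in each direction". The Group B section adds hot packs for every subject. The design has two arms and no untreated one.

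On timing, after a baseline measurement, "second assessment will be done after 2 weeks and final post assessment will be done at the end of" the twelfth session in week 4.

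The Data analysis procedure lists two families of inferential test. Between groups it plans "independent samples t test and Man Whitney test at various levels of assessment for between group comparison". Within groups it plans the following: "Freidman and repeated measure ANOVA will be performed for within group analysis separately". It does not say which family decides effectiveness.

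**The concern.** A secondary outcome needs an analysis that can answer it. This one asks whether conservative treatment works, yet every patient receives it, so no contrast between the arms can show its effect. The within-group tests are the only planned analysis left, and they ask whether the mean changes over four weeks, not why it changes.

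Patients who enter a trial because they have symptoms may improve through natural recovery or regression to the mean. A team that follows the plan as written could obtain a small p-value in each arm and report conservative treatment as effective. Nothing in the design would support that conclusion or could refute it.

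**Working it through.** **1. What each planned contrast estimates.** Write N for the effect of adding neural mobilization, C for the effect of the shared conservative treatment with hot packs, and R for natural recovery plus regression to the mean. On a simple additive view:

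- mean change in Group A = N + C + R
- mean change in Group B = C + R
- difference, A minus B = N

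The between-group difference isolates N, which is the question under Objectives. C appears only as C + R, and no planned comparison separates the two. This step needs no numerical assumption.

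**2. The plan's own figure.** The Sample size section gives 3.35±1.49 and 4.45±1.63, effect size 0.70, level 0.05, power 90% and 44 per group.

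- Pooled SD = √[(1.49² + 1.63²)/2] = 1.56
- Effect size = (4.45 − 3.35)/1.56 = 1.10/1.56 = 0.70
- The exact two-sided two-sample t calculation at 0.70 gives 44 per arm with power 90.1%.

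The stated 88 is reproduced, and it is sized on the between-group contrast.

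**3. How often a within-group test is significant when treatment does nothing.** Inputs:

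- n = 44 per arm and SD 1.56, from the Sample size section. The section does not name the scale of those figures; I treat them as pain scores.
- Pre-post correlation r and natural improvement m are assumptions, because the protocol gives neither.

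Formulas: SD of change = 1.56 × √[2(1 − r)]; noncentrality = m√44 / SD of change; two-sided 5% paired t test with 43 degrees of freedom.

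For r = 0.5 and m = 1.0:

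- SD of change = 1.56 × √1 = 1.56
- noncentrality = 1.0 × 6.633/1.56 = 4.25
- probability of significance = 98.6% in each arm, and 0.986² = 97% in both

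Chance that a given arm is significant with no treatment effect:

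| Natural improvement | r = 0.3 | r = 0.5 | r = 0.7 |
|---|---|---|---|
| 0.5 point | 42% | 55% | 77% |
| 0.75 point | 75% | 88% | 98% |
| 1.0 point | 94% | 98.6% | >99.9% |

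**4. Check with the planned type of test.** The paired test is simpler than the planned three-visit analysis. A simulation of repeated-measures ANOVA used 44 per arm, three visits, a linear improvement of 0.5 SD by week 4 (0.5 × 1.56 = 0.78 points) and no treatment effect. Each arm was significant in 70%, 83% and 97% of runs at correlations 0.3, 0.5 and 0.7. Over improvements from 0 to 1.0 SD, the rate ran from about 5% to 100%. In the same runs, the between-group t test at the final visit gave a false positive in 4.6% to 5.9%.

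**The case against.** The strongest reply is that the trial already plans the right comparison. The objective is between arms, the sample size rests on a two-group difference, and the between-group test is named first and then repeated. In a randomised trial, t or Mann-Whitney tests at each visit are valid. No sentence says that effectiveness will be judged by within-group p-values. All of this stands, and it limits the point to the secondary outcome.

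A reader might go further and infer that superiority will be claimed if one arm's within-group test is significant and the other's is not. That rule would mislead. With no true difference and a per-arm rejection rate p, the arms disagree with probability 2p(1 − p). With the paired test at r = 0.5, this is about 50% at 0.5 point, 22% at 0.75 point and 2.8% at 1.0 point. Only half of the disagreements would favour neural mobilization. But the protocol states no such rule, so these figures describe a possible misreading and not the error rate of the plan. The two hazards also work against each other: recovery large enough to make both arms look effective nearly removes disagreement between them.

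A reader might also call the lack of a group-by-time term an error. It is not. Such a model may be more efficient, but the visit-wise comparison is valid, and model detail is commonly left to an analysis plan that is not shown here.

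None of this rescues the conservative-treatment outcome. It is written into the protocol, and no further model detail can supply a comparator that the design lacks.

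**Conclusion.** The concern holds for the secondary outcome. The effect of conservative treatment cannot be estimated in this design, and the separate within-group tests cannot fill the gap. That conclusion follows from the two arms as described and rests on no assumed figure.

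The size does depend on assumptions. With natural improvement of 0.5 to 1.0 point and correlation 0.3 to 0.7, an arm would look effective in 42% to more than 99.9% of trials without any treatment effect. The central example gives 98.6%. With no natural improvement, the rate falls to the nominal 5%.

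The main comparison is sound on this point. Its validity and its 90.1% power at effect size 0.70 do not depend on the within-group tests. The point therefore ranks as one that should be fixed.

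**What to change.** 1. In Outcome measures, delete the effectiveness of conservative treatment as an outcome, or reword it as a description of change over time in the control arm.
2. In both Outcome measures and Data analysis procedure, state that conclusions on effectiveness rest only on the between-group difference. A baseline-adjusted comparison is preferable and uses baseline values already collected.
3. In Data analysis procedure, label the within-group ANOVA and Friedman results as descriptive, and report changes within each arm with confidence intervals.

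The cost is protocol wording, plus an adjusted comparison if that option is taken. No further patients, visits or measurements are needed. The trial gives up one claim, which it could not have supported.

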# **RESEARCH WORK PLAN**

Analysed (n = …)

Excluded from analysis (give reasons) (n = …)

Lost to follow-up (give reason) (n = …)

Discontinued intervention (give reasons) (n = …)

# Allocation:

# Care Providers

# Allocation :

# Patients

Assessed for eligibility=88

(n = …)

Allocated to intervention (n =44)

Received allocated intervention (n =44)

Did not receive allocated intervention (give reasons) (n = …)

Care providers (n = 1 ), teams (N = 5 ), centers (n= 1 ) performing the intervention

Care providers (n = 1 ), teams (n = 5), centers (n= 1 ) performing the intervention

Allocated to intervention (n =44)

Received allocated intervention (n =44)

Did not receive allocated intervention (give reasons) (n = …)

**questionnaire**

**SECTION 1**

**Name___________________ Study Serial No: _____________**

**Gender:** Male/ Female **Date: _______________**

**Age (Years): ______________ Occupation: ___________________________**

**Previous History of Neck Injury:** ⃝ Yes ⃝ No

**Hypertension:** Yes/No **Diabetes :** Yes/No

**Heart Disease:** Yes/No **Smoking:** Yes/ No **Surgical History: _________________**

**SECTION 2**

**NECK DISABILITY INDEX:**

This questionnaire is designed to enable us to understand how much your neck pain has affected your ability to manage in everyday life. Please answer every section and mark in each section only once, which applies to you. We realize you may consider that two of the statements in any section may relate to you, but please just mark one which most closely described your problem.

| **Section 1 : Pain Intensity** | **Pre** | **Post** |
| --- | --- | --- |
| 0. I have no pain at the movement. |  |  |
| 1. The pain is very mild at the movement. |  |  |
| 2. The pain is moderate at the movement. |  |  |
| 3. The pain is fairly severe at the movement. |  |  |
| 4. The pain is very severe at the movement. |  |  |
| 5. The pain is the worst imaginable at the movement. |  |  |
| **Section 2 : Personal Care** |  |  |
| 0. I can look after myself normally without causing extra pain. |  |  |
| 1. I can look after myself normally but it causes extra pain. |  |  |
| 2. It is painful to look after myself and I am slow and careful. |  |  |
| 3. I need some help but manage most of my personal care. |  |  |
| 4. I need help everyday in most aspects of self care. |  |  |
| 5. I do not get dressed; I wash with difficulty and stay in bed. |  |  |
| **Section 3 : Lifting (Skip if you have not attempted lifting since the onset of your neck pain)** |  |  |
| 0. I can lift heavy weights without extra pain. |  |  |
| 1. I can lift heavy weights but it gives extra pain. |  |  |
| 2. Pain prevents me from lifting heavy weights off the floor, but I can manage if they are conveniently positioned eg. On a table. |  |  |
| 3. Pain prevents me from lifting heavy weights but I can manage light to medium weight if they are conveniently positioned. |  |  |
| 4. I can only lift very light weights. |  |  |
| 5. I cannot lift or carry anything at all. |  |  |

| **Section 4 : Reading** |  |  |
| --- | --- | --- |
| 0. I can read as much as I want to with no pain in my neck. |  |  |
| 1. I can read as much as I want to with slight pain in my neck. |  |  |
| 2. I can read as much as I want with moderate pain in my neck. |  |  |
| 3. I cannot read as much as I want because of moderate pain in my neck. |  |  |
| 4. I can hardly read at all because of severe pain in my neck. |  |  |
| 5. I cannot read at all. |  |  |
| **Section 5 : Headache** |  |  |

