## Blinding:

In this study patients, assessors, data analysts will be blinded to allocation of treatment groups in this study. Except for the therapist all other staff will be kept blinded as they will not be informed about the details of allocation. Trial will be adhered to established procedures to maintain separation between staff who will collect outcome measurements and the therapist. Patient will be blinded to treatment allocation as treatment will be given in separate rooms for each group. Therapist who is not blinded will not take the outcome measurements. All the other assessors, investigators and analysts will not know the details of treatment.

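### The Neck Disability Index form sets Pre and Post columns side by side, and nothing in the protocol keeps baseline answers out of view when the later answers are given

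*Protocol*

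**What the plan says.** The Objectives section compares the two treatments "on pain intensity, cervical range of motion, disability, cervical muscle endurance and quality of life". For disability the protocol names one instrument: "Neck disability will be assessed by using neck disability index".

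The form itself is in the questionnaire at the end of the protocol. Section 1 of the questionnaire has one "Study Serial No" field and one date field ("Gender: Male/ Female Date"). Section 2 prints the NDI items once, with two answer columns against the same response options: "Section 1 : Pain Intensity | Pre | Post". The instructions speak to the patient: "Please answer every section and mark in each section only once, which applies to you".

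The timing is given under Group B (control group): "Pre assessment will be done at baseline, second assessment will be done after 2 weeks", with a final assessment at the end of the 12th session in week 4. On patient blinding, the Blinding section says: "Patient will be blinded to treatment allocation as treatment will be given in separate rooms for each group". Under Data analysis procedure, the arms are compared by independent-samples t-test or Mann-Whitney test, and change within each arm by repeated measures ANOVA or Friedman test. The Outcome measures section lists pain, endurance and range of motion as main outcomes, and the effectiveness of conservative treatment and quality of life as secondary. The NDI is in neither list.

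**The concern.** A self-report scale should record the patient's state on the day. If the earlier mark stands in the next column of the same row, the patient can answer relative to it, and the later score becomes partly a judgement of change. Any assessor who handles the sheet also sees the earlier answers.

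The protocol takes trouble to separate the therapist from outcome measurement, but it says nothing about keeping earlier NDI answers out of sight. The NDI carries the whole of the disability objective, so no second instrument would reveal a distortion. Answers given in view of the baseline mark cannot be corrected in the analysis afterwards.

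**Working it through.** **1. Does the form expose the baseline mark?**

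| Element | What the protocol shows | Bearing |
|---|---|---|
| NDI layout (Questionnaire, Section 2) | One set of items, Pre and Post adjacent | Both answers share a row |
| Identification (Questionnaire, Section 1) | One serial number, one date | No visit label and no separate form per visit |
| Instructions (Section 2) | Addressed to the patient | Points to self-completion |
| Any rule on separate sheets, covering or withholding | None found | Nothing prevents exposure |
| Assessment schedule (Group B section) | Baseline, week 2, week 4 | Two columns cannot hold three readings |

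Used as printed, the form exposes the baseline mark. That it will be used this way is an inference, because no section says the same sheet is handed back.

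**2. Where would an effect enter?**

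Let b_A and b_B be the average shift in the later NDI score caused by seeing the earlier one.

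- Within an arm: observed change = true change + b. Nothing cancels b in the within-group analyses.
- Between arms: observed difference = true difference + (b_A − b_B). If b_A = b_B, the shift cancels and the test stays at 5% under no true effect.

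The sign of b is open. A patient who expects benefit may move a box away from the visible mark. A patient who wants to be consistent may stay near it, which shrinks the recorded change.

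A difference between b_A and b_B is possible. Only Group A receives the added neural mobilization, and patient blinding rests on separate rooms, which do not hide from patients what is done to them.

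**3. Sample size used in the illustration**

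Inputs from the Sample size section: 3.35 (SD 1.49) and 4.45 (SD 1.63), alpha 0.05, power 90%.

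- Pooled SD = √((1.49² + 1.63²)/2) = 1.562
- d = (4.45 − 3.35)/1.562 = 0.704, stated as 0.70
- A two-sided two-sample t-test (noncentral t) needs 44 per arm, with power 0.904 at d = 0.704 and 0.901 at d = 0.70

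The stated 44 per arm reproduces, and the fix does not change it.

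**4. Scale, under assumed shifts**

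The protocol gives neither an NDI SD nor a bias size. Assume no true effect and a net shift δ = (b_A − b_B)/SD. With n = 44 per arm, df = 86 and the noncentrality parameter is δ√(n/2) = δ√22 = 4.690δ.

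| Assumed δ | Noncentrality | Two-sided rejection rate at 0.05 |
|---|---|---|
| 0 | 0 | 5% |
| 0.1 | 0.469 | 7.5% |
| 0.2 | 0.938 | 15.3% |
| 0.3 | 1.407 | 28.5% |

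These rates apply to any differential bias of that size, in either direction. They are not evidence that this form produces one.

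**The case against.** A reader might infer that patients will mark their final answers beside their baseline answers and that this inflates the result for Group A. The documents do not support that reading, for four reasons.

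- **Handing back the sheet is not stated.** A sheet used at two visits would need two dates, so the single date field fits a fresh copy per visit as well as one reused sheet. Two columns do not match three assessments, so the layout is an imperfect guide to practice. The Concealment of allocation section has the assessor record the post-treatment findings, so the questionnaire, which also collects medical history, may be the assessor's record form.
- **The direction is unknown.** A visible earlier mark can hide change as easily as exaggerate it.
- **An arm-specific effect of the layout is not shown.** Both arms get hot packs, isometric exercises and 12 sessions. Unequal expectation would come from weak patient blinding, and it would affect answers on separate sheets too. Only the part added by the layout counts here, and it is unknown. Assessors are meant to be blind to allocation, so their seeing baseline answers does not by itself favour an arm.
- **The NDI is in neither outcome list**, and no rule or figure in the protocol is wrong on this point.

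All four stand, and they limit the point to a possible dependence between readings. They do not remove it. Adjacent Pre and Post columns have no evident purpose if every visit gets a fresh copy, and no section keeps earlier answers out of view.

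**Conclusion.** The point holds as a modest weakness in the data-collection form. As printed, the NDI sheet allows the baseline mark to be seen when the Post answer is given, and the protocol contains no safeguard. The later reading may therefore not be independent of the first.

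This rests on one assumption, that the form is used as laid out. Any resulting shift goes straight into the within-group analyses. It biases the between-group comparison only if it differs by arm, which is possible but not demonstrated. The rates of 7.5%, 15% and 29% depend wholly on the assumed shifts of 0.1, 0.2 and 0.3 SD and are not estimates of the bias in this trial.

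Disability is in the objective and the NDI is its only measure, so the point is worth acting on. Because the NDI is outside the main and secondary outcome lists, it is a cheap improvement and not a threat to the trial's main conclusions.

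**What to change.** Replace the two-column NDI with a separate single-column sheet for each assessment (baseline, week 2, week 4). Each sheet should carry the study serial number, the visit and the date. State in the NDI section that completed sheets are collected at once, and that neither the patient nor the assessor sees earlier sheets at later visits. This also gives the week-2 reading a place on the form.

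Make the change before any post-baseline NDI is collected. Sample size, visits, treatment and analysis stay as they are. The cost is re-formatting the form, plus a few more sheets per patient to print, file and match by serial number.
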